## Methods

This study and manuscript have been designed in accordance to the Standard Protocol Items: Recommendations for Interventional Trials (SPIRIT) guidelines.

### Study design

This study is a multicenter prospective RCT with randomization into two treatment arms: (I) arthroscopic ACL repair with suture augmentation and (II) arthroscopic ACL reconstruction surgery. This study is a non-inferiority study with the hypothesis that arthroscopic ACL repair is non-inferior to (equivalent or better than) arthroscopic ACL reconstruction. All patients with proximal tears will be randomized during the operation into one of these treatment arms and will be followed up to 10-years postoperatively.

### Study sample

Potential candidates will be selected from five participating orthopaedic surgery departments, of which one is an academic hospital, three are teaching hospitals and one is a private hospital. Inclusion and exclusion criteria for participation in the study are displayed in Table 1. In general, potential inclusion involves all patients with acute, isolated, complete, proximal ACL tears that have a desire to return to pre-injury activities and exclusion involves all concomitant ligamentous and osteoarthritic injuries and skeletally immature patients. A flowchart of the study is shown in Fig. 1. Patients can withdraw their participation in this study at any time point, at which their data will be deleted.

**Table 1 Tab1:** Inclusion and exclusion criteria for participating in this trial

Inclusion criteria	Exclusion criteria

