### Goal and hypotheses

The goal of this multicenter non-inferior prospective randomized controlled trial is therefore to compare the outcomes of arthroscopic ACL repair with suture augmentation to ACL reconstruction for patients with proximal tears in a 1:1 allocation ratio. The primary outcome is the subjective International Knee Documentation Committee (IKDC) score and the secondary outcomes are other patient-reported outcomes, objective outcomes and return to sports. It is hypothesized that patients following ACL repair with suture augmentation have non-inferior primary and secondary outcomes when compared to ACL reconstruction due to the less invasive surgery.

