### Primary outcomes/endpoint (Table 2)

The primary outcome of this non-inferiority RCT is the subjective patient reported outcome (PROM) at two-year follow-up consisting of the subjective IKDC score [63] (Dutch validation [64]), as to a recent RCT on a similar topic [65, 66]. The primary endpoint is the subjective IKDC at two-years postoperatively. Patients will ultimately be followed for 10 years.

**Table 2 Tab2:** This chart provides an overview of which outcomes are collected at the different follow-up visits

	Pre	3 mns	6 mns	9 mns	1 yr	2 yrs	5 yrs	10 yrs

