### Sample size

The sample size calculation was based on the primary outcome of this study (subjective IKDC score), similar to another RCT design on this topic [65]. It has been shown that a difference of 8.8 points in the subjective IKDC score is the minimal clinically important difference (MCID) [76]. Using this non-inferiority limit of 8.8 points, and a standard deviation of 11 points [42, 65, 77] along with a two-sided alpha of 0.05, a power of 90%, and a lost-to-follow-up rate of 10%, a total of 37 patients in each group (74 patients in total) are needed to assess the primary outcome of this non-inferiority RCT. This sample size is also sufficient for the MCID of KOOS [78] and Lysholm score [79]. Given the recent studies that showed that 30-40% of the acute tears will have repairable proximal ACL tears [50, 80], we estimate that approximately 200 patients will be needed to be screened preoperatively to achieve the sample size of 74 patients [81].

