### Statistical analysis

Both an intention to treat analysis and per protocol analysis will be performed for this non-inferiority study. Comparison of nominal variables between ACL repair and ACL reconstruction will be performed using two-by-two tables with Pearson’s Chi-square test or Fisher’s exact test (in case one of the cells is < 5). For comparison of continuous variables, first tests for normal distribution of values are performed and independent t-tests are used of normal distributed values and non-parametric t-tests are used for not-normally distributed values.

A mixed model analysis for repeated measures will be performed to assess differences between both groups. Furthermore, a multivariate regression analysis will be performed for the primary endpoint of IKDC at two-years follow-up in order to correct for potential confounders. Statistical analysis will be performed using SPSS version 25.0 (IBM Software, Armonk, NY, USA). All tests are two-sided and a *p*-value of < 0.05 is considered statistically significant.

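### Deleting all data of patients who withdraw after randomisation conflicts with the planned intention-to-treat analysis and discards observed scores, failures and adverse events; the direction of any bias is not certain

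*Protocol article*

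**What the plan says.** Under Study sample, the protocol article sets the rule for withdrawal: "Patients can withdraw their participation in this study at any time point, at which their data will be deleted". It attaches no condition to the deletion. It does not separate past from future data, deletion by default from deletion on request, or efficacy scores from failure and safety records.

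Under Statistical analysis it states: "Both an intention to treat analysis and per protocol analysis will be performed for this non-inferiority study". The same section plans a mixed model for repeated measures.

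The Study design section fixes the timing: "All patients with proximal tears will be randomized during the operation into one of these treatment arms and will be followed up to 10-years postoperatively". The primary outcome section states: "The primary endpoint is the subjective IKDC at two-years postoperatively". Table 2 schedules the subjective IKDC before surgery and at seven visits from 3 months to 10 years, with failure and reoperation at every postoperative visit and adverse events at every visit. The Blinding section says that patients cannot be blinded.

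**The concern.** An intention-to-treat analysis needs every randomised patient to be accounted for in the allocated arm. A patient whose record has been deleted cannot be. If the rule is followed, the analysed set becomes the randomised patients who never withdrew, a group defined by something that happened after randomisation. The per-protocol analysis gives no protection, because the same records are missing from it.

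This matters more than usual here for two reasons. The trial is open to patients, and failure includes symptomatic instability, so a decision to withdraw may be related to how the knee is doing. The question is also one of non-inferiority, where losing poor results from the repair arm would favour the conclusion that the trial hopes to reach. Failure, reoperation and harm are counts, and each deleted event lowers the count directly.

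**Working it through.** **1. The plan's own figure.** Inputs from Sample size: "Using this non-inferiority limit of 8.8 points, and a standard deviation of 11 points", "along with a two-sided alpha of 0.05, a power of 90%, and a lost-to-follow-up rate of 10" per cent. With a true difference of zero and one-sided 0.025:

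n per arm = 2 × (1.960 + 1.282)² × 11² / 8.8² = 2 × 10.51 × 1.5625 = 32.8, so 33. Inflated for loss: 33 / 0.9 = 36.7, so 37 per arm and 74 in total.

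The stated figure reproduces. The point concerns bias and completeness, not sample size. The 10% allowance replaces lost numbers and does nothing about which patients are lost.

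**2. What the rule itself removes, by time of withdrawal.** The fair comparison is with a rule that stops collection at withdrawal but keeps what has been collected.

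- *Before year 2.* The 2-year IKDC is missing under either rule. Deletion additionally removes the interim scores and any failure, reoperation or adverse event already recorded. A patient who withdraws after the 1-year visit may have given five IKDC scores (before surgery and at 3, 6, 9 and 12 months). With retention, these enter the repeated-measures model and the analysis can rest on data missing at random given earlier scores. With deletion, the patient contributes nothing, and the analysis needs the stronger assumption that withdrawal is unrelated to outcome.
- *After year 2, before the data are analysed.* Deletion removes an observed primary-endpoint value that retention would keep.
- *After the 2-year data are analysed.* The primary result already obtained stands. Later analyses and long-term outcomes lose the patient.

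**3. Illustration of size for observed 2-year scores.** If k of 37 patients in an arm score D points below the rest of that arm, deleting them raises the arm mean by k × D / 37. The documents give neither k nor D, so both are assumptions.

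| Deleted, repair / reconstruction | D | Net shift towards repair |
|---|---|---|
| 3 / 0 | 20 | 3 × 20 / 37 = 1.6 |
| 3 / 0 | 30 | 3 × 30 / 37 = 2.4 |
| 3 / 0 | 40 | 3 × 40 / 37 = 3.2 |
| 3 / 2 | 30 | (3 − 2) × 30 / 37 = 0.8 |
| 3 / 3 | any equal D | 0 |
| 0 / 3 | 30 | −2.4 (against repair) |

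The 3 / 0 rows are 18%, 28% and 37% of the 8.8-point margin (1.62, 2.43 and 3.24 divided by 8.8). For scale, the standard error of the difference with 33 per arm is 11 × √(2/33) = 2.71.

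**4. Failure counts.** The Background cites failure rates of 6 to 9% after repair, mostly from small retrospective series. Applied to 37 patients this is 2.2 to 3.3 failures. With so few events a single deletion is visible: 3 of 37 is 8.1%, and after one failed patient is deleted it is 2 of 36, or 5.6%.

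**The case against.** The strongest reply concerns size and direction.

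A reader might infer that deletion would carry the repair arm some 2.4 points towards non-inferiority. The documents do not support this as a prediction. It needs all deletions to fall in the repair arm, whereas the rule applies to both arms and failure is an outcome for graft and repair alike. Nothing in the article shows that failed repairs withdraw more often than failed reconstructions. The shift also needs patients who had already given a 2-year score; for earlier withdrawals that score is lost with or without deletion.

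A reader might also take the 10% loss to follow-up, about four per arm, as the number of deletions. It is not a withdrawal rate. A patient who misses visits, or who has further surgery and stays in the trial, is not covered by the sentence. Likewise, a withdrawal at year 5 alters the 2-year primary result only if those data have not yet been analysed, which the article does not say.

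Finally, this is one sentence in a condensed article, and the full protocol and consent form are not shown. Deletion may in practice be on request, and reported safety events may be kept. That limits how confidently one can say that harms would be under-counted.

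All of this stands as a limit on the size claimed. It does not remove the conflict. The sentence is a stated rule, not an omitted detail, and an analysis plan cannot analyse records that have been deleted.

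**Conclusion.** The point holds. As written, the withdrawal rule and the intention-to-treat plan cannot both be followed once any patient withdraws after surgery. It would go too far to say that no intention-to-treat analysis is possible: the remaining patients would still be compared as allocated, but in an incomplete set selected after randomisation.

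The certain consequences are the loss of observed IKDC scores, of the interim scores that support the repeated-measures model, and of any events recorded for the withdrawn patients. Bias is possible, with uncertain direction. The range of 1.6 to 3.2 points against the 8.8 margin rests on three deletions in the repair arm only, all after the 2-year score, with an assumed deficit of 20 to 40 points. Balanced deletions would give about zero. The sample size is not affected.

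**What to change.** Replace the sentence under Study sample with wording to this effect: *withdrawal stops further data collection; data collected up to withdrawal are kept and analysed in the allocated arm.* Erase data only when a patient explicitly asks for it. Report withdrawals and erasures by arm, with timing and, where given, reason.

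This leaves the 33 evaluable and 37 randomised per arm, the visits and the treatments unchanged. It does not recover the 2-year score of a patient who withdraws before year 2; that remains a missing-data problem, though one with interim scores to work from.

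The cost is one amended sentence in the protocol and one in the consent form. Patients already consented keep their original terms unless re-consented. Deletion cannot be undone, so the amendment is worth more the earlier it is made.

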**Pre-operative**	
Complete primary ACL tear on physical examination and MRI	Complete ipsilateral concomitant knee ligament injury requiring surgery
Tear in proximal quarter on MRI [50, 51]	Concomitant ipsilateral knee dislocation or patellar dislocation
Age 18 – 50 years [22, 52]	Osteoarthritis KL grade ≥ 2
Preinjury Tegner level ≥ 5 & desired Tegner level ≥ 5 [53]	Previous ipsilateral ACL reconstruction/repair
Operation within 4 weeks of injury [54]	Intra-articular corticosteroids 6 months prior
	No understanding of Dutch language or not capable of understanding the study and participation
	No preoperative flexion of 90 degrees
	Grade 3 pivot shift indicating gross ligament instability that requires additional procedures
	Gross lower leg malalignment requiring bony osteotomies
	Muscular, neurological or vascular diseases that influence rehabilitation or surgery
	Prolonged use medication use of prednison or cytostatics
	Pregnancy during injury or surgery
	Osteoporosis that influence rehabilitation or surgery
**Intra-operative**	
Sufficient tissue length for retensioning to femoral insertion	No complete tear at arthroscopy or only one bundle (AM or PL) with proximal tear
Sufficient tissue quality to withhold sutures	Grade 3 or grade 4 cartilage lesions
ACL indicates anterior cruciate ligament; MCL, medial collateral ligament; LCL, lateral collateral ligament; PCL, posterior cruciate ligament; PLC, posterolateral corner.

**Fig. 1 Fig1:**
[figure not shown]
Flowchart of the REPAIR-trial

### Randomization

All patients will be consented preoperatively for the study. Patients are taken into the operating room, general or epidural anesthesia is induced, and the leg is prepped and draped for standard arthroscopic knee surgery with a tourniquet high at the upper thigh. Then standard anteromedial and anterolateral portals are created, and the knee is assessed for cartilage, meniscus and ligamentous injuries. After cartilage and meniscus injuries are addressed, the tear type of the ACL and eligibility for this study is assessed. First, it should be confirmed whether a proximal tear is present (i.e., whether the distal remnant of the ACL is of sufficient length to be reattached to the anatomical femoral footprint of the ACL) and whether sufficient tissue quality is present (i.e., whether the ligament remnant is of sufficient quality to withhold suture passage and can be tensioned towards the femur).

If these conditions are present, patients are randomized between both treatment arms, and if these conditions are not present, the patient is excluded, and standard ACL reconstruction will be performed. A computer block randomization of 10 patients per block will be done digitally prior to the study, and the allocation concealment is performed by sequentially numbered, opaque, sealed envelopes containing the name of the procedure in a randomized order. The envelopes are placed in the operating room and opened when the surgeon deems the ACL tear eligible for the study. A participant timeline is shown in Fig. 2.

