**Methods:**

This study is a multicenter prospective block randomized controlled trial. A total of 74 patients with acute proximal isolated ACL tears will be assigned in a 1:1 allocation ratio to either (I) ACL repair using cortical button fixation and additional suture augmentation or (II) ACL reconstruction using an all-inside autologous hamstring graft technique. The primary objective is to assess if ACL repair is non-inferior to ACL reconstruction regarding the subjective International Knee Documentation Committee (IKDC) score at two-years postoperatively. The secondary objectives are to assess if ACL repair is non-inferior with regards to (I) other patient-reported outcomes measures (i.e. Knee Injury and Osteoarthritis Outcome Score, Lysholm score, Forgotten Joint Score, patient satisfaction and pain), (II) objective outcome measures (i.e. failure of repair or graft defined as rerupture or symptomatic instability, reoperation, contralateral injury, and stability using the objective IKDC score and Rollimeter/KT-2000), (III) return to sports assessed by Tegner activity score and the ACL-Return to Sports Index at two-year follow-up, and (IV) long-term osteoarthritis at 10-year follow-up.

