### Surgical techniques

Prior to the start of the trial, a cadaver session will be held in order to standardize the technique of ACL repair and ACL reconstruction for all surgeons and to minimize the learning curve. All surgeons have extensive experience with ACL reconstruction and two out of five participating centers have experience with ACL repair.

The surgical technique of arthroscopic ACL repair has been more extensively described in the literature [39, 43, 55]. In brief, first the native torn ACL will be sutured with a loop using FiberWire sutures and advanced with one to two passes, so that the sutures exit the avulsed ligament towards the femur. Then, a small tunnel will be drilled from the native femoral insertion towards the lateral epicondyle using an ACL drill guide. The sutures will be passed through a TightRope button along with an additional FiberTape. The sutures and TightRope will be passed through the femoral tunnel and the button will be flipped. Then, a small tunnel will be drilled through the tibia from the anteromedial cortex towards the anterior part of the tibial footprint, and the FiberTape will be channeled through the tibial tunnel and, after cycling the knee, the FiberTape is fixed into the anteromedial cortex using a suture anchor at full extension. Finally, the repair sutures will be tensioned and tied in order to reapproximate the ACL towards the femoral footprint at 90° flexion.

For ACL reconstruction, a standard all-inside autograft hamstring tendon anatomic reconstruction technique is used [56, 57]. First, autologous hamstrings (semitendinosus and gracilis tendon) are harvested to the preference of the surgeon and will be prepared for graft usage with a minimum graft diameter of 8 mm [58, 59]. Then, femoral and tibial sockets are independently drilled in retrograde fashion using a FlipCutter drill. The graft is placed into the sockets, the knee is cycled in order to achieve optimal tension of the graft, and the graft is then fixed at the femoral and tibial side using a cortical button.

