### Blinding

Blinding for patients is not possible due to different scars, different postoperative radiographs and practical reasons. However, the data analysis will be performed in blinded fashion.

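### One fixed, published block size of 10, with envelopes opened in theatre after the surgeon's own eligibility judgement, lets a surgeon who tracks the series foresee some allocations before deciding who enters

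*Protocol article*

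**What the plan says.** All of the relevant procedure is in the Randomization section of the protocol article.

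- **Sequence:** "A computer block randomization of 10 patients per block will be done digitally prior to the study". One block size is given. The abstract sets the ratio: patients "will be assigned in a 1:1 allocation ratio", so each block holds five of each procedure.
- **Concealment:** "the allocation concealment is performed by sequentially numbered, opaque, sealed envelopes containing the name of the procedure in a randomized order".
- **Timing:** "The envelopes are placed in the operating room and opened when the surgeon deems the ACL tear eligible for the study".
- **Eligibility judgement just before opening:** the surgeon assesses whether the remnant is long enough to reach the femoral footprint, and "whether the ligament remnant is of sufficient quality to withhold suture passage and can be tensioned towards the femur". No measured threshold is given for either.
- **Consequence of a negative judgement:** "the patient is excluded, and standard ACL reconstruction will be performed".

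The Blinding section adds: "Blinding for patients is not possible due to different scars, different postoperative radiographs and practical reasons". Only the data analysis is described as blinded. The article does not say whether the five centres share one envelope series or each hold their own, and it does not mention stratification.

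**The concern.** Sealed, opaque, numbered envelopes hide the next card. They do not hide the arithmetic of a block whose size is known. Once five of one procedure have appeared in a block of ten, every remaining allocation in that block is fixed. The block size is printed in the trial's own article, and the surgeon knows every procedure he or she has performed.

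The person who may be able to foresee the allocation also makes the judgement that decides entry. If repair is expected, a borderline remnant can be declared inadequate. If reconstruction is expected, the same remnant can be accepted. A rejected patient receives reconstruction outside the trial, and the unopened envelope stays next in line.

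Two features make this matter more here than in many trials.

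- Remnant quality bears mainly on the result of repair. The article's Background links poor tissue quality to worse repair outcomes, and its Discussion relies on strict selection for tissue quality. Keeping poor remnants out of the repair arm only would make repair look better, and so push towards non-inferiority.
- The exclusion happens before randomisation. Both planned analysis sets (Statistical analysis section) begin after that step.

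**Working it through.** **Inputs from the article.** Block size 10, ratio 1:1, 74 patients, five centres. **Assumption:** recruitment is about equal, that is 15, 15, 15, 15 and 14 per centre.

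**The plan's own total.** With margin 8.8, SD 11, two-sided alpha 0.05 and 90% power:

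n = 2 × (1.960 + 1.282)² × 11² / 8.8² ≈ 32.8, so 33 per arm; 33 / 0.9 = 36.7, so 37 per arm and 74 in total.

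This agrees with the Sample size section. The point does not affect the sample size.

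**One full block of size 2m, with the size known and all earlier allocations seen.**

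- Expected number of allocations known with certainty: 2m / (m + 1). For m = 5: 10 / 6 = 1.67 of 10, or 16.7%.
- Expected correct guesses, always naming the arm that is behind: m + (2^(2m) / C(2m, m) − 1) / 2. For m = 5: 5 + (1024 / 252 − 1) / 2 = 6.53 of 10, or 65.3%. Chance gives 50%.

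**If each centre has its own series.** Each centre completes one block and starts a second that stops after four or five patients. No allocation can be certain before the sixth place in a block, so only the five complete blocks contribute:

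- Certain: 5 × 1.67 = 8.3 of 74, or about 11%. A simulation of 20,000 trials gave 8.34.
- Correct guesses: 62% in the same simulation. The unfinished blocks pull the figure below 65.3%.

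**If one series served all centres and one observer could follow it in full.** There are seven complete blocks and a remainder of four:

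- Certain: 7 × 1.67 = 11.7 of 74, or about 16%.
- Correct guesses: about 65% (simulated).

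A surgeon in one of five hospitals is unlikely to see that whole series, so this is an upper bound.

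**Would a smaller fixed block help?** The same formulas give:

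| Fixed block size | Certain | Correct guesses |
|---|---|---|
| 4 | 33% | 70.8% |
| 6 | 25% | 68.3% |
| 8 | 20% | 66.6% |
| 10 | 16.7% | 65.3% |

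No: a smaller block of known size is more predictable.

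**Varying sizes.** With per-centre lists mixing sizes 4, 6 and 8 (chosen only for illustration), naming the arm that is behind is still right about 66% of the time. What largely disappears is certainty, because a surgeon who does not know the sizes generally cannot tell where a block ends.

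**The case against.** The case on the other side has real force.

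**Foreknowledge is conditional.** A surgeon must track every earlier envelope in the same series. The article does not say how many surgeons operate at each centre, and several sharing a series would each see only part of it unless they compared notes. Nothing suggests that anyone intends to do this. That stands, and it is why the figures above are ceilings for a fully informed observer. What remains is that the design permits selection.

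**A reader might infer that surgeons can predict allocations in general.** The figures do not support that. At most about one allocation in six is certain, and the rest are guesses only moderately better than a coin toss.

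**A reader might also infer that arm is confounded with centre**, since "two out of five participating centers have experience with ACL repair" and no stratification is mentioned. The article does not support this either.

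- Silence on stratification in a condensed article does not show that there is none.
- The two harms largely need opposite set-ups. Following the series is practical when each centre holds its own envelopes, and blocks of 10 then keep the arms within five patients of each other at every centre. Centre imbalance needs one shared list, which a single surgeon can hardly follow.
- Even under a shared list the imbalance would be due to chance. In the two experienced centres (30 patients assumed) it averages 3.4 patients. At its 95th percentile the share of each arm treated there differs by 22 percentage points. For assumed centre effects of 3, 5 and 8.8 IKDC points, that shifts the comparison by 0.6, 1.1 and 1.9 points, against a margin of 8.8, and it could be adjusted for.
- Unequal experience with repair exists within centres whatever the list, so stratification would not remove it. The article also plans a cadaver session to standardise both techniques.

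The centre argument therefore reduces to a request for clarification.

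**Conclusion.** The point holds in a limited form. A fixed, published block size, envelopes opened in theatre, an operator who cannot be blinded and an unmeasured eligibility judgement immediately beforehand are all stated in the article. Together they leave room for selective entry that no planned analysis can undo.

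The size is modest but not negligible for 37 patients per arm: about 8 of 74 allocations certain and about 62% guessed correctly. This rests on separate series of about 15 patients per centre, knowledge of the block size and full tracking of the series. The bound per complete block is 1.67 of 10 certain.

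The size of any resulting bias in the IKDC score cannot be derived from the article, because it depends on how often remnants are borderline and on how surgeons behave. Its direction, if borderline remnants were refused when repair was expected, would favour non-inferiority. This is a worthwhile, cheap improvement and does not by itself invalidate the design.

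**What to change.** 1. Replace the fixed block with randomly varying block sizes that are not disclosed to surgeons and do not appear in investigator-facing documents. Do not simply shrink the fixed block.
2. Release each allocation centrally, by web or telephone, only after the intra-operative eligibility decision has been irrevocably recorded. This stops the decision being revised once the arm is seen. It does not prevent guessing beforehand, so it complements step 1.
3. Log every intra-operative exclusion with its reason, by centre, and report the log, so that selective rejection would be visible.
4. State whether the lists are per centre or shared.

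**Cost:** a small set-up cost for a new list and a randomisation service, and dependence on an online or telephone system during surgery. No additional patients are needed; the total stays at 74.
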